##### Extended tally sheets

As part of quality control, in all four arms at two time points, during the 18-month implementation and test period (months 3 and 15), providers will complete extended tally sheets on two separate days in each month. The extended tally sheets will include an identifying code of the provider but no identifying code of the patient. The extended tally sheet will include additional information from the patient on alcohol knowledge,^71^ social norms^72^ and health literacy^73^ applied to alcohol, as it informs the content of advice given; and, additional information from the provider on contextual characteristics that informed their advice giving. The extended tally sheets will include a consent form for the patient and self-completed additional questions for the patient to complete, once the consultation has ended.

##### Self-completed additional questions by patient

On two separate days, during months 3 and 13, coinciding with and following the consultation with the provider using the extended tally sheet, patients who are able to read and write will be invited to give consent to self-complete additional questions to the extended tally sheet in the waiting room before leaving the PHCU, handing the completed tally sheet and questions to a researcher in attendance. No patient identifying information will be included in the questionnaires. Six domains, serving as quality control, will be included:

AUDIT-C.^65^PHQ-2.^67^Experiences of the consultation.Views on being asked about alcohol consumption.Health literacy^73^ as it applies to alcohol.Exposure to communication and media campaigns on alcohol.

On each day, 270 patient questionnaires will be collected across all PHCUs, with up to 1080 (540 during each of months 3 and 13) questionnaires completed in total across the 4 days.

##### Provider-based attitudes and experiences

At two time points during the 18-month implementation period (months 3 and 13), providers will provide data on their attitudes and experiences to working with patients with heavy drinking and comorbid depression, online supplementary file S1, online supplementary file S2.

Providers will complete a short questionnaire after each of the booster training sessions that they attended (at months 4 and 8). The specific content, number and timing of the training-related questionnaires will depend on the study arm: Arm 2 and 3 participants will fill in one questionnaire after the booster session; while Arm 4 participants will fill in two after each of the two booster sessions.

##### Observations

The training sessions with the PHC providers, and the meetings of the CABs will be observed by a neutral observer in order to take note of additional possible barriers in the implementation of the protocol that emerge through the training sessions and meetings. Participant responsiveness will also be observed.

### Economic data for return-of-investment analyses

Within SCALA, we will conduct return-on-investment (RoI) analyses, by assessing for each EURO invested in scaling up delivery of screening and brief interventions in PHC in Columbia, Mexico and Peru, how many EUROs will be saved by reductions in future healthcare utilisation. The return of investment will be defined as the (return on investment=(gain from investment–cost of investment)/cost of investment). For details on the data required for RoI analyses, online supplementary file S1, online supplementary table S5.

For the RoI analyses, the effects of increased coverage of alcohol brief advice among PHC patients will be modelled using effect sizes from previous meta-analyses.^52 74^ To translate the reduced intake of alcohol into health gains, we will calculate alcohol-attributable fractions for major disease and injury categories. These fractions will then be applied to the cost data outlined in online supplementary file S1, online supplementary table S5 to estimate the alcohol-attributable costs per disease category.

### Process evaluation

As the intervention is embedded in a complex system involving actions and actors at different levels (individual, organisational and municipal), a thorough process evaluation will be carried out to complement and better understand the outcomes. Through the process evaluation, the implementation with its fidelity and adaptation will be assessed, along with the drivers of scale-up and contextual factors influencing the implementation, the drivers and the outcomes. This will be achieved in four blocks: driver diagram creation; barriers and facilitators analysis; assessment of implementation, mechanisms of impact and context and further contextual and policy analysis.

#### Key informant interviews

A number of individual or group interviews will be undertaken throughout the project with key stakeholders—providers, UP members, CAB members, municipal and PHC-based clinical leaders, project partners and any other people involved in the implementation of the SCALA project. Depending on the stakeholder and their involvement in the project, the topics of the interviews will cover topics such as the necessary adaptation to the protocol; the experience of implementing the programme in PHC practice and the perception of the municipal support and the community campaigns.

#### Driver diagrams

Driver diagrams^75^ will be used in order to describe the intervention and its causal assumptions, providing the theory of change through displaying what contributes to intervention aim and what are the relationships between primary drivers, secondary drivers and specific change ideas/activities. The initial general driver diagram, online supplementary file S1, online supplementary figure S3, will be modified based on local contexts and adapted throughout the duration of the project in order to understand how scale up varies in the different cities.

#### Barriers and facilitators assessment

Factors influencing the implementation of the SCALA protocol will be assessed before the implementation, as well as monitored throughout. The anticipated barriers and facilitators to implementation will be assessed through development of evaluation tool based on literature review^76–78^ and implementation framework,^62^ with subsequent refinement and adaptation to the local context through focus group discussions and workshops with the CABs. The aim of the tool is to identify the barriers that would have to be addressed and monitored throughout implementation and the facilitators that would incentivise and engage providers and the primary healthcare unit (PHCU) managers in uptake and scaling up of the SCALA protocol. The experienced barriers and facilitators will be further monitored through meeting observations, provider questionnaires and interviews, as well as interviews with other involved stakeholders (eg, CAB members, PHCU managers).

#### Implementation, mechanisms of impact and context

The factors influencing the progress from scale-up to outcomes will be identified and documented based on UK Medical Research Council guidance,^79^ analysing factors within five groups: (1) description of intervention and its causal assumptions, (2) implementation, (3) mechanisms of impact, (4) context and (5) outcomes. All aspects of the intervention will be taken into consideration: the intervention, intervention tailoring, training, training tailoring, as well as the municipal action, consisting of the CABs and the communication campaign, combining both quantitative and qualitative methods in order to obtain a comprehensive picture of the integration and interaction of included variables. A detailed description of the topics of interest and accompanied methods is presented in online supplementary file S1, online supplementary table S6.

The five groups will be assessed as follows:

Description of the intervention. The description of the intervention and its causal assumptions draws from the previously described driver diagram.Implementation. Delivery of the training will be assessed though document analysis (reports from training), observation and self-reports from the trainers. Delivery of the intervention will be assessed through document analysis, interviews with patients and providers. The areas of focus will be fidelity, adaptation, dose and reach. Implementation of the CAB meetings and community action will be assessed mainly through document analysis, as well as key informant interviews.Mechanisms of impact. The following three areas will be covered: participant responses to the intervention, mediators and unintended consequences. Mechanisms of impact of intervention delivery will be assessed through patient and providers’ questionnaires. The patient interviews will focus on their responsiveness to the intervention, specifically looking at perceived acceptability. In order to evaluate participants’ responses to the training, a post-training questionnaire examining satisfaction with the training and perceived utility of training sessions will be applied, triangulated with data from observation and trainers’ self-report. Additionally, providers’ self-efficacy will be tested as potential mechanism of impact that links the implementation to the outcomes. Mechanisms of impact of the CAB meetings and community action will be examined through key informant interviews and questionnaires. Specific focus will be placed on perceptions and mechanisms of actions of the communication campaign, examining its effect on attitudes and social norms of both providers and patients.Context. Contextual factors that should be considered in order to better understand the success of the intervention will be assessed through meeting observation, document analysis and provider questionnaires, as well as stakeholder interviews, with the main focus primarily on individual and organisational level characteristics of the context. For the training evaluation, context will be assessed through observation and trainers’ self-report. Context of municipal level actions will be assessed through key informant interviews. Additionally, contextual and policy factors on national and municipal levels will be assessed as described below.Outcomes. The data collected through process evaluation will be combined with the outcomes and presented within the Reach, Effectiveness, Adoption, Implementation and Maintenance framework,^80–82^ evaluating SCALA’s impact across the dimensions of reach, effectiveness, adoption, implementation and maintenance.

#### Contextual and policy factors

Based on methodology of Ysa *et al*,^83^ contextual and policy factors on national and municipal level will be identified through document analysis and key informant interviews. The main variables considered for contextual analysis will be: (1) available data similar to that of the OECD better life initiative;^84^ (2) Sustainable Governance Indicators^85^ and (3) World Values Survey data.^86^ For policy analysis, the information sought will be for a for alcohol policy-related strategies, action plans, legislation and evaluations, both on country and municipal levels. The existing contextual and policy factors will be mapped onto the test of the scale-up of the SCALA package to describe and identify those factors on national and municipal level that might influence going to full scale beyond the tested scalable units.

### Outcomes

#### Primary outcome

The primary outcome will be the cumulative proportion of the number of adults (aged 18+ years) registered with the PHCU that have their alcohol consumption measured with a completed AUDIT-C instrument during the study period (coverage). The number of adults registered is provided by the administrative office of the PHCU and includes all adult patients covered by the PHCU, whether or not they consult during the 18-month implementation test period.

#### Secondary outcomes

Proportion of consulting patients who have their alcohol consumption measured by AUDIT-C: calculated as the number of adults who have their alcohol consumption measured by AUDIT-C divided by the total number of adults who consult the PHCU during the same time period per participating provider and per PHCU.At risk population receiving advice and/or treatment for heavy drinking: calculated as the number of adults with an AUDIT-C score of 8+ who receive brief advice and/or referral for their heavy drinking divided by the total number of patients with an AUDIT-C score of 8+ per participating provider and per PHCU. Information will also be collected on the number of patients with an AUDIT-C score of <8 who receive brief advice and/or treatment for their heavy drinking.Proportion of patients with AUDIT-C score of 8+ who receive assessment for depression: calculated as the number of consulting adults with an AUDIT-C score of 8+ who complete PHQ-2 divided by the total number of patients with an AUDIT-C score of 8+ per participating provider and per PHCU.At risk population receiving advice and/or treatment for comorbid depression: calculated as the number of adults with a PHQ-2 score of 3+ who receive a patient leaflet and/or referral for their depression divided by the total number of patients with a PHQ-2 score of 3+ per participating provider and per PHCU.Provider attitudes: attitudes of the participating providers will be measured by the SAAPPQ.^65^ The responses will be summed within the two scales of role security and therapeutic commitment. Individual missing values for any of the items in a domain will be assigned the mean value of the remaining items of the domain before summation.

### Statistical tests of key hypotheses

#### Primary study goal

Multilevel regression analyses will be undertaken at 12 months’ time of the implementation test period, using cumulative results at months 1 to 12, and at 18 months’ time using cumulative results months 1 to 18. Both analyses will include covariates of country and results during baseline month, analysed at the levels of the PHCU by study arm, taking into consideration the hierarchical nature of the data. For any PHCU that drops out during the study, outcome values for subsequent measurement points will be set at the last value obtained.

##### Hypothesis 1

Municipal action leads to more sustainable coverage among PHCU that receive training. We will compare results on primary outcome after 18 months with results after 12 months between Arm 3 versus Arm 2 via regression.

Dependent variables:

For each PHCU, cumulative results of months 1–18 of number of patients whose alcohol consumption is measured with AUDIT-C per 1000 registered patients; and cumulative results of months 1–12 per 1000 registered patients.

Random effects:

Country as random intercept (test for inclusion).

Independent variables:

Proportion of consulting patients who have their alcohol consumption measured with a completed AUDIT-C instrument during the baseline measurement month.Condition:Municipal action (yes vs no).Covariate:Proportion of consulting patients who have their alcohol consumption measured with a completed AUDIT-C instrument during the baseline measurement month.

It is postulated that coverage for Arm 3 will be significantly higher than for Arm 2.

##### Hypothesis 2

Training leads to higher coverage than no training. For both months 1–12 and months 1–18, compare cumulative coverage as per primary outcome between Arms 1 and 2 via multilevel regression analyses.

Dependent variable

Cumulative results months 1–12, and cumulative results months 1–18 of number of patients whose alcohol consumption is measured with AUDIT-C per 1000 registered patients withPHCU.

Random effects:

Country as random intercept (test for inclusion).

Independent variables:

Condition:Training (Arm 2 vs Arm 1).Covariate:Proportion of consulting patients who have their alcohol consumption measured with a completed AUDIT-C instrument during the baseline measurement month.

It is postulated that coverage for Arm 2 will be significantly higher than for Arm 1.

##### Hypotheses 3

In the presence of municipal action, the short clinical package and short training do not lead to less coverage than the standard clinical package and standard training. In the presence of clinical equivalence of a relative difference of cumulative coverage of patients screened by less than 10% by month 6, the difference between Arm 3 (all 15 PHCU across the three countries) and Arm 4 (all 12 PHCU across the three countries) will be assessed with regression analyses. If Arm 4 is not superior to Arm 3, both arms will be collapsed into Arm 3 (shorter package) from month 8 onwards.

Dependent variable:

Cumulative results months 1 to 6 per 1000 patients.

Random effects:

Country as random intercept (test for inclusion).

Independent variables:

Condition:Length of clinical package (longer=Arm 4 vs shorter=Arm 3).Covariate:Proportion of consulting patients who have their alcohol consumption measured with a completed AUDIT-C instrument during the baseline measurement month.

It is postulated that Arm 4 is not significantly superior to Arm 3.

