The third and final barrier concerns the cost of implementing measurement and brief-advice for heavy drinking in PHC setting. Although, alcohol advice and treatment programmes can lead to substantial reductions in healthcare costs,^16^ freeing considerable numbers of working age people from alcohol-related diseases,^19^ their initial implementation can require a significant time-commitment on the part of providers, in terms of both initial training requirements and the time taken to deliver advice in routine practice. The largest part of the costs of implementing measurement and brief advice for heavy drinking in PHC settings are directly caused by the time spent by the healthcare providers delivering this intervention.^53^ Moreover, this large amount of time is experienced by healthcare providers as an important barrier to deliver routine measurement and brief advice to their patients.^54^ As evidence suggests that shorter sessions of brief advice are not less effective compared with longer sessions,^52 55 56^ it seems that reducing the time spent by healthcare professionals in preparing for these sessions could be a viable strategy to increase the overall adoption and implementation of alcohol measurement and brief advice at PHC level.

Given the strong comorbidity between heavy drinking and depression, our protocol includes screening for depression for those patients identified as heavy drinkers, with appropriate referral or PHC support for treatment.^57–59^

In the SCALA study, we implement three interventions (independent variables) for the PHCU:

Intensity of clinical package and training (standard, vs short, vs none).Training of providers (present, vs absent).Community integration and support (municipal action present, vs absent).

The main outcome (dependent variable) is the cumulative proportion of the adult (aged 18+ years) population registered with the PHCU that has their alcohol consumption measured within the 18-month implementation test period (defined as coverage). Three hypotheses are to be tested.

### Hypothesis 1

Municipal action leads to more sustainable coverage. After 18 months, the difference in coverage between municipal action present and municipal action absent for those PHCU that receive training is larger than after 12 months.

### Hypothesis 2

In the absence of municipal action, PHCU that have received training obtain higher coverage than PHCU that do not receive training.

### Hypothesis 3

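### No term listed in the Hypothesis 1 regression tests whether the Arm 3 v Arm 2 gap is larger at 18 than at 12 months, and none uses the pairing within PHCU

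*Protocol article*

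**What the plan says.** In the Introduction, Hypothesis 1 concerns a change in a gap, with month 18 set against month 12: "the difference in coverage between municipal action present and municipal action absent for those PHCU that receive training is larger than after 12 months".

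Under Statistical tests of key hypotheses, the Hypothesis 1 entry says: "We will compare results on primary outcome after 18 months with results after 12 months between Arm 3 versus Arm 2 via regression". The listed specification is:

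- **Dependent variables (plural):** one is given as "For each PHCU, cumulative results of months 1–18 of number of patients whose alcohol consumption is measured with AUDIT-C per 1000 registered patients"; the other is the same count accumulated to month 12 only.
- **Random part of the model:** a single entry, "Country as random intercept (test for inclusion".
- **Condition:** "Municipal action (yes vs no".
- **Covariate:** the share of consulting patients measured in the baseline month.
- **Prediction:** "It is postulated that coverage for Arm 3 will be significantly higher than for Arm 2".

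The opening of the same section describes one multilevel analysis at 12 months and one at 18 months, "analysed at the levels of the PHCU by study arm, taking into consideration the hierarchical nature of the data". The sample size section gives 96.5% power for Arm 3 v Arm 2 with 15 PHCUs in each arm.

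**The concern.** Hypothesis 1 carries the sustainability claim, and it is a difference of differences. To test it, a model needs a within-PHCU change as outcome or an arm-by-time term. The printed list has neither, and its prediction is about level. A trial could therefore report Hypothesis 1 as confirmed because Arm 3 exceeds Arm 2 at both times, without having examined whether the gap grew.

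The second issue is dependence. The months 1–12 count is contained in the months 1–18 count, so the two values from one PHCU are strongly correlated. Any comparison of 18 with 12 months gains its precision from that pairing, and a country intercept does not carry it. The same random-effects line is adequate for Hypotheses 2 and 3, where each model can have one row per PHCU. Hypothesis 1 is the only one that sets two time points on the same PHCUs against each other.

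**Working it through.** **1. The plan's own power figure, and what it covers.** Inputs from the sample size section: coverage 0.075 (Arm 2) and 0.15 (Arm 3), ICC 0.03, 15 000 adults per PHCU, 15 PHCUs per arm, 5% significance.

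- Design effect: 1 + 14 999 × 0.03 = 450.97.
- Effective n per arm: 15 × 15 000 / 450.97 = 498.9.
- SE (unpooled): √[(0.075 × 0.925 + 0.15 × 0.85) / 498.9] = 0.01987.
- Power (two-sided): Φ(0.075 / 0.01987 − 1.96) = Φ(1.82) = 96.5%.

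The figure reproduces. It is the power for a difference in level, built on the 12-month coverage assumptions. No 18-month coverage enters it.

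**2. Assumptions for the rest.** The protocol gives no within-PHCU correlation ρ between the two cumulative values. Independent equal monthly increments would give √(12/18) = 0.82; I use 0.5 to 0.95, with the same variance at both times. The ICC implies a between-PHCU SD of 1000 × √[0.03 p(1 − p)] per 1000: 46 at p = 0.075 and 62 at p = 0.15, so about 54. The protocol does not give the extra gain in months 13–18 either. If the assumed 12-month gap of 75 per 1000 grew at the same rate, it would add 75 × 6/12 = 37.5 per 1000.

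**3. Separate regressions at 12 and 18 months.** One row per PHCU. In simulations with 15 v 15 PHCUs, country as a fixed effect and one covariate, the 18-month regression rejected a true null 4.6–5.6% of the time. Size is correct, but the 18-v-12-month contrast does not appear in either model.

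**4. Both values stacked, listed terms only.** The arm effect averages two correlated rows, so its true variance is (1 + ρ) times the one assumed. Size = 2[1 − Φ(1.96/√(1 + ρ))].

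| ρ | 0.5 | 0.7 | 0.8 | 0.9 | 0.95 | →1 |
|---|---|---|---|---|---|---|
| Formula | 11.0% | 13.3% | 14.4% | 15.5% | 16.0% | 16.6% |
| Simulated | 11.3% | 13.3% | 14.9% | 17.0% | 17.2% | – |

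The formula ignores the general rise in coverage from month 12 to 18. With no time term, a rise g inflates the residual variance by 1 + g²/(4 SD²). At g = 37.5 and SD 50 that is 1.14, and the formula falls to 8.7% at ρ = 0.5 and 13.9% as ρ nears 1. A time term removes this dilution.

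**5. Arm-by-time term added, no PHCU effect.** The true variance of the contrast is now (1 − ρ) times the one assumed. Size = 2[1 − Φ(1.96/√(1 − ρ))] = 0.6% at ρ = 0.5 and effectively zero at 0.8. For an extra gain d, with SD 54:

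- True SE = 54 × √[2(1 − ρ) × 2/15]; assumed SE = 54 × √(4/15) = 27.9.
- Paired power = Φ(d / true SE − 1.96).
- Unpaired power = Φ[(d − 1.96 × 27.9) / true SE].

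At ρ = 0.8 and d = 37.5 the true SE is 12.5. Paired power is Φ(1.05) = 85%; unpaired power is Φ(−1.38) = 8%.

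| ρ | Paired, d = 37.5 | Unpaired, d = 37.5 | Paired, d = 25 | Unpaired, d = 25 |
|---|---|---|---|---|
| 0.5 | 48% | 19% | 24% | 7% |
| 0.8 | 85% | 8% | 52% | 1% |
| 0.95 | >99% | 0.3% | 98% | 0% |

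Simulation at d = 37.5 with SD 50 gave 50%, 86% and >99% paired, and 25%, 17% and 8% unpaired. Comparing two separate gaps as if they were independent makes the same error.

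**The case against.** The strongest reply is that the section's opening describes two analyses, one per time point, each at PHCU level. With one row per PHCU, a PHCU intercept cannot be separated from the residual, and country is the only level left to list. Hypothesis 2 names the same two periods with the same random effect, and nobody would read that as stacking. Covariance detail is also commonly left to a statistical analysis plan or full protocol, neither of which is shown.

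Much of this stands. A reader might infer that 30 PHCUs will be analysed as 60 independent rows, so that the type I error is inflated. The text never says so. The plural outcome heading and the sentence comparing 18 with 12 months lend that reading some support, but separate regressions are at least as natural. A reader might also take the low power as a property of the plan. It is not: it needs an arm-by-time term, or a comparison of two gaps as independent, and the plan lists neither. A per-PHCU change score is not excluded by the wording, though it is not stated.

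The reply does not rescue the test of Hypothesis 1. On the reading most favourable to error control, the defining contrast is absent. Nor is this mere brevity: the article prints outcomes, random effects, condition and prediction for this hypothesis, and together they describe a comparison of levels.

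**Conclusion.** The concern holds in this form: the analysis listed for Hypothesis 1 does not test the hypothesis as the Introduction defines it, and nothing listed uses the pairing within PHCU. That conclusion needs no numerical assumption.

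The consequence depends on a choice the protocol leaves open. Separate regressions have correct size (about 5%) and leave the contrast untested. Stacking with the listed terms gives a municipal-action test that rejects about 11–17% of the time at nominal 5% for ρ from 0.5 to near 1, somewhat less if an unmodelled general rise in coverage is large. An arm-by-time term without a PHCU effect gives a very conservative test that loses most of its power at the higher correlations. The size of that loss rests on ρ, the SD and the months 13–18 gain; the protocol gives neither ρ nor that gain, so no single figure should be quoted. The stated 96.5% is correct for the level difference and does not apply to this contrast.

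**What to change.** For Hypothesis 1, do one of the following:

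- Regress one change score per PHCU (month-18 minus month-12 cumulative coverage, that is, the coverage added in months 13–18) on municipal action, the baseline proportion and country.
- Fit both time points jointly with time, an arm-by-time term and a PHCU random intercept (or an unstructured within-PHCU covariance), and test the arm-by-time term. Adding a PHCU intercept alone is not enough, because the model would still estimate an average level.

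Reword the prediction as a larger Arm 3 v Arm 2 gap at 18 than at 12 months. State in the sample size section that 96.5% is for the level difference; if power for the contrast is quoted, give it over a range of ρ and of months 13–18 gains. The single-time-point regressions for Hypothesis 2 can stay as they are.

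The cost is a few lines of text. Coverage is already collected monthly, so no new data are needed.
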